## Abstract

**Background:**

Atrial fibrillation (AF) is an independent risk factor for stroke and a significant predictor of mortality. Evidence-based guidelines for stroke prevention in AF recommend antithrombotic therapy corresponding to the risk of stroke. In practice, many patients with AF do not receive the appropriate antithrombotic therapy and are left either unprotected or inadequately protected against stroke. The purpose of the Global Anticoagulant Registry in the FIELD (GARFIELD) is to determine the real-life management and outcomes of patients newly diagnosed with non-valvular AF.

**Methods/design:**

GARFIELD is an observational, international registry of newly diagnosed AF patients with at least one additional investigator-defined risk factor for stroke. The aim is to enrol 55,000 patients at more than 1000 centres in 50 countries worldwide. Enrolment will take place in five independent, sequential, prospective cohorts; the first cohort includes a retrospective validation cohort. Each cohort will be followed up for 2 years. The UK stands to be a significant contributor to GARFIELD, aiming to enrol 4,582 patients, and reflecting the care environment in which patients with AF are managed. The UK protocol will also focus on better understanding the validity of the two main stroke risk scores (CHADS_2_ and CHA_2_DS_2_VAS_C_) and the HAS-BLED bleeding risk score, in the context of a diverse patient population.

**Discussion:**

The GARFIELD registry will describe how therapeutic strategies, patient care, and clinical outcomes evolve over time. This study will provide UK-specific comprehensive data that will allow a range of evaluations both at a national level and in relation to global data and contribute to a better understanding of AF management in the UK.

**Trial registration:**

ClinicalTrial.gov: NCT01090362

## Background

Atrial fibrillation (AF) is the most common clinically significant arrhythmia in the adult population; it is an independent risk factor for stroke and mortality. People with AF have a fivefold increased risk of stroke and a twofold increased risk of death [1]. Prevalence of AF increases throughout life, affecting less than 1% of individuals under 60 years, approximately 4% of individuals over 60 years, and up to 10% of over those aged 80 years [2,3].

The estimated diagnosed prevalence of AF in the UK is around 1.4% [4,5], and more than 46,000 new cases of AF are diagnosed every year [6]. About 15% of all strokes are caused by AF, and 12,500 strokes each year in England are thought to be directly attributable to AF [7]. Furthermore, AF-related strokes are more serious: they are more likely to be fatal than strokes in patients without this arrhythmia; among patients who survive, these strokes cause more disability with less likelihood of independent recovery [8]. For example, findings from the Framingham study indicate that mortality is increased 1.84-fold in strokes in people with AF compared to those in sinus rhythm, and recurrence is more frequent [9]. The Copenhagen stroke study found that patients with AF require longer hospital stays (50 days versus 40 days, P < 0.001) and a lower discharge rate to their own homes (odds ratio 1.7; 95% confidence interval [CI] 0.44 to 0.85) with poorer neurological and functional outcomes [8]. Further, data from the European community stroke project show that AF increased by 50% the probability of remaining disabled (odds ratio 1.43; 95% CI 1.13 to 1.80) or handicapped (odds ratio 1.51; 95% CI 1.13 to 2.02) [10].

Management of AF requires either a rate-control strategy to slow the ventricular rate or a rhythm-control strategy in an attempt to maintain sinus rhythm. Regardless of whether the rate-control or the rhythm-control strategy is pursued, antithrombotic therapy for prevention of stroke and thromboembolism is a fundamental management tool.

Oral anticoagulants are effective in the reduction of stroke and thrombolytic events among patients with AF. Vitamin K antagonists (VKAs) are the most widely used anticoagulants and adjusted-dose warfarin has been shown to reduce the risk of stroke by approximately 60% in patients with AF [9]. However, in practice the use of VKAs is not universal [10]. As a result, only about one-half of the patients who should receive antithrombotic therapy to prevent thromboembolic stroke actually receive it [11].

Risk stratification is important when considering anticoagulation, as the risk of stroke in AF patients is dependent on clinical predictors [12]. A recent stroke risk stratification scheme, CHA_2_DS_2_-VASc (Cardiac failure, Hypertension, Age ≥75 [Doubled], Diabetes, Stroke [Doubled] – Vascular disease, Age 65–74 and Sex category [Female]), has been proposed as an alternative to CHADS_2_[13]. CHA_2_DS_2_-VASc adds further variables to CHADS_2_ – age 65–74, female sex, and vascular disease, and thromboembolism in addition to stroke/ transient ischaemic attack (TIA).

Anticoagulant therapy carries a risk of bleeding, and major bleeding such as intracranial bleeds can be catastrophic. Bleeding risk-stratification schemes assess the risk of major bleeding for patients on anticoagulation to help determine the risk–benefit balance in AF. A novel bleeding risk score – HAS-BLED (Hypertension, Abnormal renal/liver function [1 point each], Stroke, Bleeding history or predisposition, Labile international normalised ratio [INR], Elderly [>65], Drugs/alcohol concomitantly [1 point each]) [14] – is gaining recognition internationally [12] and in the UK, and could potentially improve assessment of bleeding risk in patients with AF.

In 2006 the National Institute for Health and Clinical Excellence (NICE) published guidelines for the management of AF, with priorities on identification and diagnosis of AF, treatment of AF, and provision of antithrombotic therapy [15]. One of the key recommendations of the guidelines is a formal assessment of the risk of thromboembolism using a stroke risk stratification and thromboprophylaxis algorithm (Figure 1). The guideline proposes routine anticoagulation with warfarin for patients at high risk of stroke, and aspirin for those at low risk of stroke.

**Figure 1 F1:**
[figure not shown]
**NICE stroke risk stratification and thromboprophylaxis algorithm [**[15]**].** Reproduced with permission.

The prevalence of AF in the UK is increasing, probably due to the ageing population and improved survival from conditions predisposing to AF, including, for example, myocardial infarction. A large population-based study of the epidemiology and treatment of AF in the UK found prevalence of diagnosed AF rose steadily (0.84% in men in 1994 compared with 1.49% in 2003, compared with 0.83% and 1.29%, respectively, in women) [4]. The number and proportion of AF patients in the UK prescribed antithrombotic therapy has progressively increased over time [4,16]. An analysis of national data from 1994 to 2003 found under one-half of all AF patients received any antithrombotic treatment in 1994 but around 80% received some sort of stroke prevention in 2003 [4]. Also, treatment of AF with oral anticoagulants more than doubled from 1994 to 2003 in men (25% to 53%) and has increased significantly women (32% to 40%) [4]. However, the use of anticoagulants remains inappropriate [4,17] and the NICE 2006 costing report estimated that 46% of patients who should be on warfarin are not receiving it [18]. There is also evidence to suggest underuse of anticoagulation in the elderly; for example, in one study elderly patients (age >85 years) were less likely to initiate warfarin (relative rate 0.16, 95% CI 0.15 to 0.18) and more likely to start aspirin (relative rate 1.66, 95% CI 1.47 to 1.88) compared with patients aged 40–64 years [17].

Much of the UK evidence is based on retrospective cross-sectional studies and was derived from prevalence data. As such, there is limited evidence on persistence of treatment with antithrombotic therapy and it has been indicated that only 60% of patients prescribed warfarin continue for at least 2 years [17]. Also, much of the available evidence relates to AF management prior to the publication of the NICE guidelines in 2006. It is not clear how well clinicians adhere to these guidelines and what impact this has had. There is an absence of contemporary longitudinal data on the clinical management of AF in the UK, including the key therapeutic area of antithrombotic therapy, persistence of therapy, and related clinical outcomes.

### Importance of GARFIELD UK

The Global Anticoagulant Registry in the FIELD (GARFIELD) is an observational, international, longitudinal registry of patients newly diagnosed with AF at risk of stroke, and aims to determine real-life treatment patterns and clinical outcomes. The global study aims to recruit 55,000 patients in five sequential cohorts of 10,000 patients each, alongside a validation cohort of 5000 patients. The methods for the global study have been published [19]. The UK is the only country undertaking GARFIELD to have its own protocol; the UK protocol was developed from the global protocol and adapted to the UK context to maximise the value of GARFIELD to the UK. It therefore has a slightly different design and includes important and original specific research questions relevant to the UK population. Tailoring the protocol to the UK allowed it to be adopted by the Primary Care Research Network portfolio of research. A number of publications will emanate from the UK-specific data over the course of the study to provide real-life contemporary evidence. As such, this paper is an important point of reference for the UK study. Principally, the UK study will review the management of AF in the UK and evaluate clinical practice against guideline recommendations.

## Methods/design

### Study design

GARFIELD in the UK is primary care based and aims to recruit 4,582 patients at more than 100 sites across the UK. Enrolment will take place in five independent sequential cohorts, parallel to the global study. Similar to the global study, Cohort 1 will include a retrospective validation cohort of patients diagnosed with AF between 6 months and 24 months previously. Data will be extracted through a case notes review at baseline, and at every 4 months until 24 months after diagnosis. The data will be collected using an electronic case report form (eCRF). A summary of the UK study design is provided in Figure 2.

**Figure 2 F2:**
[figure not shown]
Summary of UK study design.

### Study aims

The key aims of the GARFIELD registry are to determine the real-life treatment patterns and clinical outcomes of newly diagnosed patients with non-valvular AF with at least one additional risk factor for stroke.

In accordance with the global objectives, the study will assess the rate of stroke and systemic embolisation, and assess the outcome of these events with specific reference to:

• The incidence and characteristics of bleeding complications (e.g. location and severity, classified as major, clinically relevant non-major, and minor);

• Therapy persistence, including discontinuation, interruption, and changes of therapy regimen;

• For patients on VKAs, fluctuations in the INR over time.

The UK protocol has additional objectives that will inform the management on AF. GARFIELD in the UK seeks to evaluate the performance of the novel stroke risk score CHA_2_DS_2_-VASc in comparison with CHADS_2_ in predicting stroke risk in the UK study population. Likewise it will evaluate the effectiveness of the bleeding risk score HAS-BLED in predicting bleeding risk within the UK study population. In addition, the study will determine the clinician and patient factors associated with the decision to anticoagulate patients. Another unique objective of the UK study is to determine any variations in levels of anticoagulation associated with ethnicity. Furthermore, the study will determine where patients are principally diagnosed with AF and assess the role of primary care in the management of AF in the UK.

### Study setting

In the UK, all healthcare delivery is centred on the general practitioner (GP), with referrals for specialists and for routine admission to hospital organized at the GP level. As a result of the National Health Service structure, GPs maintain in their surgeries a complete medical history of their patients. Recruiting from the general practices will therefore capture all patients diagnosed with AF regardless of their care settings, and in the UK, these include hospital departments (cardiology) and emergency settings. The UK is therefore recruiting solely from the primary care setting; nevertheless, we expect to achieve a representative sample of patients with AF being cared for in the UK, comparable to the sample recruited in the global study.

Investigator sites (GP practices) will be representative of the UK, and will include sites in England, Wales, Scotland, and Northern Ireland, with the aim of achieving a sample representative of the geographical distribution of the UK population. Practices will be recruited and trained in collaboration with national research networks. The Primary Care Research Network (PCRN) England provides a world-class infrastructure to conduct clinical research in primary care settings in the NHS by supporting and facilitating recruitment and set up of sites. PCRN England is delivered through eight local research networks that cover the whole of England. Similar networks operate in Scotland (Scottish PCRN), Northern Ireland (Northern Ireland Clinical Research Network), and Wales (National Institute for Social Care and Health Research). Expressions of interest will be sent to practices by the research network for each region, and sites will be selected from the responses received.

### Registry population

The details of the registry population are given in full in the global GARFIELD methods paper [19].

#### Prospective cohorts

The eligibility criteria for the prospective cohorts are: patients aged 18 years or older with a diagnosis of non-valvular AF within the past 6 weeks and at least one additional risk factor for stroke [19].

#### Retrospective cohort

The eligibility criteria for the retrospective cohort are: patients with a diagnosis of non-valvular AF within the 6–24 months before enrolment, and at least one additional risk factor for stroke [19].

### Patient recruitment

Each participating GP will identify eligible patients using a search of the computerised clinical record and will invite them by standard letter to be enrolled in the GARFIELD registry. GPs will also opportunistically inform patients in the practice and give them a participant invitation letter and information sheet.

For the retrospective cohort, a practice computer search for all patients with a current diagnosis of AF (between 6 months and 2 years prior to inclusion) will be undertaken. Once identified, patients will be assessed according to the inclusion/exclusion criteria and eligible patients invited to participate.

For the prospective cohort, a computer search will be undertaken at least once a month at each practice to identify newly diagnosed patients with non-valvular AF. Once identified, the patient will be assessed according to the inclusion/exclusion criteria. Eligible patients will be sent a participant invitation letter and information sheet and asked to contact the practice if they are interested in participating. A screening log of all patients invited to participate in the registry will be maintained at each site. A consent visit is arranged for interested patients, after which they are enrolled in the registry and baseline data are completed.

### Collection of baseline and follow-up data

Data collected at baseline include: demographics (e.g. ethnicity, sex, date of birth); body mass index; vital signs at diagnosis; AF symptoms; type of AF (new, paroxysmal, persistent, permanent); method and site of diagnosis; treatment strategy initiated at diagnosis; antithrombotic therapy; treatment decision (patient and physician factors); and medical history (cardiovascular, medical, bleeding).

Follow-up data include clinical events (stroke/TIA, peripheral embolism, acute coronary syndrome) and outcome of event; AF-related medical consultation and/or hospitalisation and outcome; AF treatment change; change in antithrombotic therapy (discontinuation, duration on therapy, reasons for discontinuation); bleeding events (classified as major, clinical relevant non-major, and minor); bleeding location of treatment (e.g. Accident and Emergency, GP practice); outcome of bleeding (recovered, permanently disabled, fatal); bleeding healthcare utilisation (hospitalisation, Accident and Emergency, physician, etc.); medical history update; mortality, including sudden cardiac death and non-cardiovascular death; and INR records in relation to therapeutic range, and location of INR monitoring.

### Clinical outcomes and data quality

The study outcomes comprise clinical events (stroke, TIA, systemic and pulmonary embolism, myocardial infarction), bleeding events, therapy persistence, hospital visits and INR monitoring, and are listed in below:

• Cerebrovascular events defined as stroke including:

– Primary ischaemic stroke

– Primary intracerebral haemorrhage

– Secondary haemorrhagic ischaemic stroke

• TIAs

• Systemic embolism

• Pulmonary embolism

• Mortality

• Acute coronary syndromes including:

– Unstable angina

– ST-elevation myocardial infarction

– Non-ST-elevation myocardial infarction

• Bleeding events including:

– Frequency

– Location

– Severity (classified as major [clinically overt bleeding associated with a fall in haemoglobin of ≥2 g/dl OR a transfusion of ≥2 packed red blood cells or whole blood OR a critical site: intracranial, intraspinal, intraocular, pericardial, intra-articular, intramuscular with compartment syndrome, retroperitoneal OR a fatal outcome], clinical relevant non-major and minor)

• Therapy persistence, including:

– Rate of discontinuation

– Duration of time on therapy

– Reasons for discontinuation

– Duration and cause of treatment interruption or suspension

• Analysis of events listed with regard to hospitalisation and outcomes

• Any other hospital visits (inpatient, outpatient, emergency department)

• Major adverse cardiac events

• For patients treated with VKA:

– Frequency and timing of monitoring required in maintaining therapeutic anticoagulation

– INR recordings in relation to therapeutic range

– Location of INR monitoring and medical consultations due to INR testing

– Use of bridging anticoagulation necessitated by VKA interruption

– Outcomes in relation to INR fluctuation.

Source data verification will be undertaken in 20% of all cases to verify adherence to the protocol and assess the level and accuracy of data recording.

### Sample size and data analysis

The total projected sample size for the UK is 4,582, comprising 417 retrospective patients for Cohort 1 and 833 prospective patients for Cohorts 1 to 5. With these projected sample sizes the precision of estimated incidence of stroke is set out in Table 1 for different levels of incidence.

**Table 1 T1:** Precision of estimated incidence of stroke for different levels of incidence, and confidence intervals on effect sizes for quantitative measures

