	**Width of 95% confidence interval**		
**Expected incidence of stroke**	**Sample size of retrospective patients: 417**	**Cohort size of prospective patients: 833**	**Total sample size of 4,582**
2.5%	±1.5%	±1.1%	±0.5%
5%	±2.1%	±1.5%	±0.6%
10%	±2.9%	±2.0%	±0.9%
20%	±3.8%	±2.7%	±1.2%
30%	±4.4%	±3.1%	±1.3%
40%	±4.7%	±3.3%	±1.4%
50%	±4.8%	±3.4%	±1.4%
Width of 95% confidence interval			
Sample size of retrospective patients: 417		Cohort size of prospective patients: 833	Total sample size of 4,582
0.14		0.10	0.04

An interim analysis will be done at the UK level for the baseline data in each cohort and after all patients in each of the first four cohorts have completed the study. For a full analysis, baseline data, follow-up data, and study endpoint data will be summarised overall and by treatment groups, cohort, and region. Summaries of categorical data will be presented as frequency counts, percentages, and 95% confidence intervals. Continuous data will be presented as means (standard deviations), medians (with 95% confidence intervals), interquartile ranges, minimum, maximum, and number of patients.

Comparison of follow-up and outcome data between treatment groups, cohorts, and regions will be made using linear (for continuous outcomes) or non-linear (for categorical outcomes) mixed modelling with practice included as a random effect. Association between outcome variables and baseline data will be explored using the same method. For continuous data, normality of residuals will be tested using the Kolmogorov–Smirnov test and transformation or bootstrapping will be implemented where required. Time-to-event analysis will use Kaplan–Meier and Cox regression analyses to summarise and explore the association with baseline and other pertinent data. Comparison of CHADS_2_, CHA_2_DS_2_VASc, and HAS-BLED risk measures will be compared on the basis of receiver-operating characteristic curve analyses. The baseline characteristics of the patients – who have been classified as at risk of stroke according to physician-perceived risk factors or combinations of factors – will be reported.

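### Retrospective patients had to survive 6–24 months to be enrolled, yet they count in the overall and apparently the Cohort 1 outcome estimates, which understates mortality and fatal events

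*Protocol article*

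**What the plan says.** All references are to the protocol article.

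- **Sample size and data analysis:** the UK target is 4,582 patients in all, described as "comprising 417 retrospective patients for Cohort 1 and 833 prospective patients for Cohorts 1 to 5". The section continues: "With these projected sample sizes the precision of estimated incidence of stroke is set out in Table 1 for different levels of incidence". The columns of that table are for 417, for 833 and for the total of 4,582.
- **Retrospective cohort:** eligible are "patients with a diagnosis of non-valvular AF within the 6–24 months before enrolment" with at least one further stroke risk factor.
- **Patient recruitment:** these patients are found by "a practice computer search for all patients with a current diagnosis of AF (between 6 months and 2 years prior to inclusion". They are then checked for eligibility and invited.
- **Study design:** the retrospective validation group is placed inside Cohort 1. On follow-up: "Data will be extracted through a case notes review at baseline, and at every 4 months until 24 months after diagnosis".
- **Analysis text after Table 1:** baseline, follow-up and "study endpoint data will be summarised overall and by treatment groups, cohort, and region". Follow-up and outcome data are also compared between cohorts by mixed models, and time-to-event data are analysed by Kaplan–Meier and Cox methods.
- **Clinical outcomes and data quality:** mortality is a listed outcome, and a fatal outcome is one criterion for a major bleed.

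**The concern.** A retrospective patient enters only if still alive when the practice runs its search, 6–24 months after diagnosis. The recorded history nevertheless starts at diagnosis. Over the interval from diagnosis to enrolment, death is impossible by design, and a fatal stroke or fatal bleed cannot appear. Prospective patients face the same condition for at most 6 weeks.

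If the two kinds of patient share one denominator, deaths and fatal events are undercounted. The overall figure moves a little, because the retrospective patients are 9.1% of the total. Cohort 1 moves more, because they are a third of it. The abstract says that the registry will describe how outcomes evolve over time, and Cohort 1 is the starting point of that series. A Cohort 1 mortality that is too low because of sampling would look like a worsening in Cohorts 2–5.

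**Working it through.** **1. Does the total contain the retrospective patients?** 417 + 5 × 833 = 417 + 4,165 = 4,582. Yes. Their share is 417/4,582 = 9.1% of all patients and 417/(417 + 833) = 417/1,250 = 33.4% of Cohort 1.

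**2. Table 1 reproduced.** Half-width = 1.96 × √(p(1 − p)/n). At p = 5%:
- n = 417: 1.96 × √(0.0475/417) = 2.1%
- n = 833: 1.5%
- n = 4,582: 0.63%, printed as 0.6%

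All 21 stroke-incidence entries reproduce to one decimal, so the last column is computed on the pooled total.

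**3. Mortality.** The article gives no mortality rate, so true two-year mortality m is varied. Assumptions: constant hazard λ = −ln(1 − m)/24 per month, and time from diagnosis to enrolment E uniform on 6–24 months among those diagnosed. Only patients alive at E can enter, so each E is weighted by S(E) = exp(−λE). The mortality that this group shows by month 24 is

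[∫ S(E) dE − 18 × S(24)] / ∫ S(E) dE, with both integrals from 6 to 24.

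For m = 10%: λ = 0.00439, S(6) = 0.9740 and S(24) = 0.9. The integral is (0.9740 − 0.9)/0.00439 = 16.86. The result is (16.86 − 16.20)/16.86 = 3.9%.

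- Cohort 1, if pooled: 0.334 × 3.9% + 0.666 × 10% = 8.0%
- Overall: 0.091 × 3.9% + 0.909 × 10% = 9.4%
- Later cohorts against Cohort 1: 10/8.0 = 1.25

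| True two-year mortality | Retrospective group | Cohort 1 if pooled |
|---|---|---|
| 5% | 1.9% | 4.0% |
| 10% | 3.9% | 8.0% |
| 15% | 6.0% | 12.0% |
| 20% | 8.1% | 16.0% |

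Across this range the retrospective group shows about 40% of the true mortality, and Cohort 1 reads about 20% too low.

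**4. Stroke incidence.** The article gives no stroke case fatality. Suppose that 20–50% of strokes before enrolment keep the patient out. A true 5% then reads 4.4–3.5% in the retrospective group. Pooled:
- 0.091 × 4.4% + 0.909 × 5% = 4.95%
- 0.091 × 3.5% + 0.909 × 5% = 4.86%

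The shift is 0.05–0.14 points, against a half-width of ±0.63.

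A simulation with stroke and non-stroke death as separate hazards, with and without frailty, gives the same picture. At 25–50% case fatality the retrospective stroke proportion is about 9–30% too low in relative terms, and the pooled figure about 1–3% too low. If no stroke were fatal, the crude retrospective proportion would be 1–7% too high in relative terms, because these patients were selected to survive and so are at risk for longer.

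**5. Cost of using prospective patients only.** √(4,582/4,165) = 1.049, so half-widths grow by about 5%.

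| Incidence | n = 4,582 | n = 4,165 |
|---|---|---|
| 2.5% | ±0.45% | ±0.47% |
| 5% | ±0.63% | ±0.66% |
| 10% | ±0.87% | ±0.91% |
| 50% | ±1.45% | ±1.52% |

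**The case against.** The strongest reply is that stroke incidence, the quantity Table 1 is built on, hardly moves. A shift of 0.05–0.14 points lies well inside ±0.63, and the large distortion concerns mortality, for which the article states no precision. That stands. A reader might infer that all event rates, stroke included, are biased downward. The documents do not support this, because they give no stroke case fatality and the sign for stroke depends on it. Only for death and fatal events is the direction certain.

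It can also be said that Table 1 gives the retrospective patients their own column and labels the per-cohort column as prospective patients. By-cohort results may therefore be meant to be prospective only. This is a fair reading, and no test of retrospective against prospective patients is named. But the study design puts the retrospective group inside Cohort 1, and the analysis text compares cohorts without excluding it. The Cohort 1 figures above therefore hold only if the 417 are analysed there. Their place in the 4,582 does not depend on that reading.

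Three further inferences go beyond the text:
- **Kaplan–Meier and Cox analyses ignore delayed entry.** The article is silent on entry time, which can be left to the analysis plan. Silence is not a decision.
- **The retrospective group cannot serve as a validation cohort.** The article never says what is to be validated and refers to the global methods paper for the population.
- **Patients too disabled to consent are lost.** The consent visit is described only for prospective patients. For the retrospective group the text says only that they are invited. Being alive is required; the rest is plausible but not stated.

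**Conclusion.** The point holds for mortality and fatal events and should be fixed. Selection on survival, data collection from diagnosis, inclusion in the total of 4,582 and the overall endpoint summary are all stated in the article, so this is a stated choice and not omitted detail. With a true two-year mortality of 10%, the retrospective group would show about 3.9% and the overall estimate about 9.4%. Cohort 1 would show about 8.0% if the 417 are analysed within it, enough for later cohorts to appear about 25% worse with no real change. These sizes rest on assumed mortality, constant hazards and uniform entry over 6–24 months. The downward direction for mortality does not depend on the particular rates. For pooled stroke incidence the effect is minor and of uncertain sign.

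**What to change.** 1. State that overall and by-cohort estimates of incidence, mortality and survival use the 4,165 prospective patients, with Cohort 1 represented by its 833.
2. In the stroke-incidence part of Table 1, replace the 4,582 column by n = 4,165: ±0.5, 0.7, 0.9, 1.2, 1.4, 1.5 and 1.5% for incidences of 2.5, 5, 10, 20, 30, 40 and 50%.
3. Report the 417 retrospective patients separately. For mortality and time-to-event analyses they enter the risk set at enrolment; events before enrolment are described only.

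The cost is a change of wording and one table column, with no new data. Half-widths become about 5% wider (at 5% incidence, ±0.63% to ±0.66%). The retrospective group loses usable follow-up: under uniform entry, mean entry is at 15 months, which leaves about 24 − 15 = 9 of 24 months per patient.

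### Table 1 gives precision as if patients were independent although they are clustered in GP practices, so its half-widths are too narrow, mainly in the pooled n = 4,582 column

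*Protocol article*

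**What the plan says.** Under Sample size and data analysis, the protocol article breaks its planned UK total of 4,582 patients down as "comprising 417 retrospective patients for Cohort 1 and 833 prospective patients for Cohorts 1 to 5". It then says: "With these projected sample sizes the precision of estimated incidence of stroke is set out in Table 1 for different levels of incidence". Table 1 lists ± half-widths of the 95% confidence interval for incidences from 2.5% to 50%, in columns for n = 417, 833 and 4,582. It mentions no ICC, design effect or other allowance for practice.

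Under Study design, the UK study "aims to recruit 4,582 patients at more than 100 sites across the UK", and Study setting explains that the sites are GP practices. The text after Table 1 plans comparisons between treatment groups, cohorts and regions by "mixed modelling with practice included as a random effect", with the same method for associations with baseline data. For description, "Summaries of categorical data will be presented as frequency counts, percentages, and 95% confidence intervals"; the article does not say how those intervals will be computed.

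**The concern.** The same section takes two positions on clustering. The comparison models allow for patients of one practice being more alike than patients of different practices. The precision table sets that similarity to zero. If it is positive, a sample gathered through practices carries less information about a UK incidence than the same number of independent patients, and the printed half-widths promise more than the design delivers. The loss grows with the number of patients per practice, so it should be largest in the pooled column, where the table looks most precise. At stake is the accuracy of the only precision statement in the article.

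**Working it through.** **Inputs from the article.** n = 417 (retrospective), 833 (each prospective cohort) and 417 + 5 × 833 = 4,582 (total); 95% confidence, so z = 1.96; incidences as in Table 1; more than 100 practices.

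**Step 1: reproduce Table 1.** Half-width = 1.96 × sqrt(p(1 − p)/n).

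- n = 417, p = 5%: 2.09%, printed ±2.1%
- n = 833, p = 20%: 2.72%, printed ±2.7%
- n = 4,582, p = 5%: 0.63%, printed ±0.6%
- n = 4,582, p = 50%: 1.448%, printed ±1.4%

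All 21 incidence cells agree to the printed decimal. The separate row for quantitative measures (0.14, 0.10, 0.04) matches 1.96 × sqrt(2/n) = 0.136, 0.096, 0.041, also without a clustering term. The steps below concern the incidence cells only.

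**Step 2: could rounding hide a design effect?** In the tightest pooled cell (p = 50%), the largest value that prints as 1.4 is 1.45, so the design effect can be at most (1.45/1.448)² ≈ 1.003. The corresponding limits are about 1.006 for n = 417 and 1.013 for n = 833. No meaningful allowance is hidden in the table.

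**Step 3: add clustering.** Design effect DE = 1 + (m − 1) × ICC, with m = n / number of practices; the half-width is multiplied by sqrt(DE). The ICC is not in the article, so 0.001 to 0.05 is an assumption. With 100 equal practices, m = 45.8 for the total. Because the article says more than 100, this is an upper bound on the mean practice size. With 150 practices, m = 30.5.

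Pooled sample, incidence 5% (±0.63% under independence):

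| ICC | DE, 100 practices | Effective n | Half-width | Widening | DE, 150 practices | Half-width |
|---|---|---|---|---|---|---|
| 0.001 | 1.04 | 4,385 | ±0.65% | 2% | 1.03 | ±0.64% |
| 0.005 | 1.22 | 3,743 | ±0.70% | 11% | 1.15 | ±0.68% |
| 0.01 | 1.45 | 3,164 | ±0.76% | 20% | 1.30 | ±0.72% |
| 0.02 | 1.90 | 2,416 | ±0.87% | 38% | 1.59 | ±0.80% |
| 0.05 | 3.24 | 1,414 | ±1.14% | 80% | 2.48 | ±0.99% |

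**Step 4: the smaller columns.** This assumes that all 100 practices contribute to each cohort.

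- n = 833 (m = 8.3): DE 1.01 to 1.37, widening 0.4% to 17%; at 5% incidence, ±1.48% becomes ±1.49% to ±1.73%. At ICC 0.01 it is ±1.53%, which still prints as ±1.5%.
- n = 417 (m = 4.2): DE 1.00 to 1.16, widening 0.2% to 8%; at 5% incidence, ±2.09% becomes ±2.10% to ±2.25%. At ICC 0.01 it is ±2.12%, which still prints as ±2.1%.

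**Step 5: unequal practices.** With a coefficient of variation (CV) of practice size, DE = 1 + ((1 + CV²)m − 1) × ICC. For an assumed CV of 1, ICC 0.01 and m = 45.8, DE = 1 + (91.6 − 1) × 0.01 = 1.91 instead of 1.45. The article gives no practice-size distribution, so this only shows the direction.

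**The case against.** The strongest defence is that the effect may be small where the table applies. Its rows are headed "Expected incidence of stroke". Stroke is a rare event, and its within-practice correlation may be low; at ICC 0.001 to 0.005 the pooled half-width at 5% incidence moves only from ±0.63% to between ±0.65% and ±0.70%. The two smaller columns barely change at low ICC. This stands, and it limits the size of the point. It does not remove the inconsistency, since any positive ICC widens every incidence cell.

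Three stronger readings are tempting, and the article does not support them.

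- **That Table 1 is miscalculated.** It is not; every incidence cell is right under independence.
- **That the study is too small.** Precision is presented as a consequence of the projected numbers. Those numbers are about one-twelfth of the global targets under Importance of GARFIELD UK (10,000/833, 5,000/417 and 55,000/4,582 are each about 12.0). No recruitment target is derived from the table.
- **That the reported intervals, the Kaplan–Meier and Cox analyses or the INR analyses will ignore correlation and under-cover.** The article mentions these in a line each and does not say that practice is left out or that a patient effect is excluded. A condensed article commonly leaves such detail to the full protocol or analysis plan.

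**Conclusion.** The point holds as a moderate issue of stated precision. The independence built into Table 1 conflicts with the practice random effect in the same section, and the direction of the error is certain for any positive ICC. Its size cannot be fixed from the article. It rests on the assumed ICC range and on practices of equal size, with 100 practices giving the upper mean cluster size. On those assumptions the pooled column is where the change matters: anything from negligible to an 80% widening, with the lower part of the range the more plausible for stroke. The n = 833 and n = 417 columns need little more than a caveat.

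**What to change.** Restate the Table 1 incidence half-widths multiplied by sqrt(1 + (m − 1) × ICC), for a stated ICC range and expected number of patients per practice, and say that the present figures are the independence case. If practice sizes are expected to differ widely, use the unequal-size form of the design effect. State that 95% confidence intervals for the descriptive incidences and percentages will use practice-level variance (cluster-robust or from a random-effect model), so that they agree with the mixed models; if the full plan already says this, a cross-reference is enough.

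The cost is a revised table, one or two sentences, and slightly less favourable stated precision. No additional patients or data are needed, because the planned models already require practice to be identified.
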